#### Usual care

There is currently no single model for ERS in the UK, but the predominant modes of delivery involve referral to a programme (eg, 10–12 weeks) of structured, supervised exercise at an exercise facility (eg, gym or leisure centre) or a counselling approach to support patients to engage in a variety of types of physical activity.^11^ ERS operate diversely to accommodate patient choice and local availability of facilities, the common goal being to reduce the risk of long-term metabolic, musculoskeletal and mental health conditions due to physical inactivity. The three participating sites were selected from different regions of the UK (different ERS providers) to provide diversity of approach; the schemes are described in table 3.

**Table 3 T3:** Characteristics of the local ERS involved in the study

	South West England (predominantly Plymouth)	West Midlands (Birmingham)	Greater Glasgow and Clyde (GGC) Health Board Area
Population of city/locality and general characteristics	264 000 93% White British. Average age is 39 years. Plymouth has higher than average levels of poverty and deprivation (26.2% of population among the poorest 20.4% nationally). Life expectancy, at 78.3 years for men and 82.1 for women, is the lowest of any region in the South West of England.	1 244 438 White British (53.1%), Pakistani (13.5%) and Indian (6%). Birmingham is ranked the sixth most deprived local authority in the UK. Approximately 40% of the population lives in highly deprived areas. The average life expectancy in Birmingham is 77.1 years for males and 81.9 years for females.	1 161 370 GGC is the largest health board in the UK, comprising six local authority areas: 92.5% white, 5.3% Asian, Asian Scottish or Asian British, 1.2% African, 0.2% Caribbean or black, 0.4% mixed, 0.4% other. There is large variation in deprivation across GGC, but as a whole, it experiences higher than average levels of deprivation and poverty (34.4% population among the poorest 12.4% national average). Life expectancy at 74.9 years for males and 80.0 years for females, is the lowest in Scotland.
Number of centres/facilities where referrals are made to in the ERS	One main ERS run by Everyone Active in Plymouth and two smaller ones in rural locations. Referrals for ERS came from 31 local GP practices.	One main ERS, Be Active Plus run by Birmingham City Council Wellbeing Service. Referrals for ERS came from 286 local GP practices.	One main ERS (Live Active) delivered by six local leisure trusts in six local authority areas of GGC (Glasgow, East Renfrewshire, Renfrewshire, East Dunbartonshire, West Dunbartonshire and Inverclyde). Referrals are possible from any health professional in primary and secondary care.
Weeks, sessions and general details about ERS	Schemes vary from 6 to 12 weeks, attendees should commit to a minimum of two sessions/week in the gym with drop-in swimming, aquafit and gentle exercise group sessions available to all. All ERS referrals are risk assessed as low or medium risk. Those classed at medium risk may only attend a supervised session. Additionally, a ‘walking for health’ scheme is highlighted by one ERS provider.	Patients meet with a health and fitness advisor to discuss their preferences for physical activity and an individually tailored 12-week exercise programme is designed for them. Activities include the use of gyms, swimming, fitness classes, badminton and table tennis. The gyms are local authority or privately owned. Privately owned gyms are obliged to offer their facilities to Be Active Plus participants. Patients are also told about activities such as the use of parks and open spaces in Birmingham and walking to work, etc. Participants are also contacted after 3 and 6 months and a report is sent to their GP at their 12-week exit interview.	Patients meet with an ERS advisor for behavioural change support and to design a suitable physical activity plan. Patients are given information on a variety of physical activity options including those offered by leisure centres (eg, fitness classes, swimming, gym, etc) as well as health walks, home exercise, active travel, apps, etc and are able to offer specialist guidance on activities suitable for those with medical conditions and/or disabilities. Patients assessed as high risk at referral are screened by a cardiologist prior to being accepted to the scheme. There are fixed contact points of 1, 3, 6 and 12 months, but patients can choose how often they wish support (telephone, email or face-to-face) from the advisor in addition to these over a 12-month period.
Cost for patients in ERS (if applicable)	Costs vary related to age/concessions. 3 months ERS costs between £14.90 and £70 inclusive of all activities. Pay as you go: £2.10–£3.50 per session.	Patients are not charged for their assessment and support by the health and fitness advisor. The costs of the programme depend on chosen activities and leisure centre attended. Patients in receipt of state benefits or tax credits are eligible for a Passport to Leisure which entitles them to a 30% discount on most activities offered at Birmingham City Council run leisure centres, well-being centres and swimming pools. They can attend free Be Active sessions which take place at restricted times in leisure centres.	Live Active behavioural support is free to the patient for 12 months. If patients wish to use leisure facilities, they are entitled to access this at a concessionary rate (usually around 30% reduction).
Number of people referred to local ERS from 1 August 2015 to 31 March 2017 (ie, during the recruitment period of the study)	300	3470	6500
Most common primary reason for referrals (1 August 2015 to 31 March 2017)*	Depression/anxiety/stress: 24%	BMI>30: 28%	BMI≥30: 58%

*The data on primary reason for referral are subjective as many patients have multiple conditions and a practitioner may favour recording one condition (eg, obesity) rather than another (eg, low mood). Within the respective schemes, the quality of recording the referral reason also appears to be variable.

BMI, body mass index; ERS, exercise referral scheme; GP, general practitioner.

### Determination of sample size

In the absence of a published minimally important difference for MVPA, assuming a ‘small’ to ‘moderate’ standardised effect size of 0.35, we estimated that 413 participants are required at 88% power and a two-sided alpha of 5% assuming 20% attrition, or 90% power at a two-sided alpha of 5% allowing for 16% attrition (using ‘sampsi’ in STATA V.14). Given that the intervention is being delivered at the level of the individual participant, clustering has not been factored into the sample size calculation. Based on the baseline SD for MVPA total weekly minutes in ≥10 min bouts of 104–113,^33^ an effect size of 0.35 would correspond to a between-group difference of 36–39 min of MVPA per week.

### Measures

#### Primary outcome measure

The primary outcome is the number of weekly minutes of MVPA, in ≥10 min bouts, measured objectively by GENEActiv Original accelerometer,^34^ over 1 week at 12 months post-randomisation compared with the control group. To be included participants need to provide activity recorded over 4 days, including a weekend day, for at least 16 hours/day.

#### Additional measures

Total weekly minutes of MVPA in ≥10 min bouts, measured objectively by accelerometer, over 1 week at 4 months.Achievement of at least 150 min of MVPA, measured objectively by accelerometer, over 1 week at 4 and 12 months.Achievement of at least 150 min of MVPA over 1 week using the self-reported 7-day Physical Activity Recall Questionnaire at 4 and 12 months.Self-reported weekly minutes of MVPA at 4 and 12 months.Average daily hours of sedentary behaviour measured objectively by accelerometer over 1 week at 4 and 12 months.Self-reported average daily hours of sleep over 1 week at 4 and 12 months.Self-reported health-related quality of life, assessed by the EQ-5D-5L^35^and SF-12v2^36^ at 4 and 12 months.Self-reported symptoms of anxiety and depression, assessed by the Hospital Anxiety and Depression Scale^37^ at 4 and 12 months.Uptake of the ERS by participant self-report at approximately 4 weeks and at 4 months, and from ERS records.Adherence to physical activity, using a composite measure to describe the proportion in each arm of the trial that achieved at least 150 min of MVPA in bouts of at least 10 min at 4 months and were still doing so at 12 months.

#### Self-reported survey process measures

Single and multiple items, using Likert scales, to assess self-efficacy/confidence to be physically active, importance of being physically active, relatedness (perceived frequency and availability of support), perceived autonomy/control over physically active choices, involvement in self-monitoring and planning to do physical activity.In the intervention group, measures of engagement with e-coachER including whether or not the participant visits the website at least once, and whether they reach a stage of the online support to indicate they have set and reviewed at least one physical activity goal. Experience from engagement with other LifeGuide online interventions suggests there may not be an optimum dose of engagement.

#### Economic evaluation

Cost-effectiveness. Incremental cost of the intervention to the NHS and incremental cost per change in minutes of MVPA (in ≥10 min bouts) and per QALY.An economic evaluation of e-coachER will be undertaken using NHS, personal social services, and patient perspective. The analysis will be twofold—short-term (within-trial) cost-effectiveness analysis (from baseline to 12 months postrandomisation) and long-term cost-effectiveness analysis (beyond-trial modelling of long-term expectations for cost-effectiveness), for e-coachER against ERS. The main outcome of the economic analysis will be an incremental cost per QALY (based on EQ-5D-5L). The short-term cost-effectiveness analysis will use resource use data for development of training of and input from a local LifeGuide facilitator, and central LifeGuide technician; provision and running of the exercise sessions at leisure centres and health and personal social service use. Data will be collected using the e-coachER monitoring system, key informant interviews (including trial manager), review of trial management records and participants’ questionnaires at baseline, 4 and 12 months. Unit costs will be taken from the NHS reference costs (eg, DH 2015/2016),^38^ standard unit costs^39^ and published literature. The long-term cost-effectiveness of e-coachER will be based on an existing policy-relevant decision analytical model.^40 41^ The analysis will account for the impact of physical activity on lifetime risk of developing coronary heart disease, stroke and type 2 diabetes.

### Process evaluation

The barriers to, and facilitators for, recruitment will be explored with participants in the early stages of the trial through qualitative interviews with local researchers at each site, and also via local researcher field notes of conversations with participants at various stages of the trial. Along with relevant supporting literature, this information will be used to optimise recruitment during the remainder of the trial.

Following guidelines for evaluating complex interventions,^42^ a nested mixed methods process evaluation will be undertaken, focussing on identifying factors relating to recruitment, engagement, acceptability, mechanisms and fidelity.

The assessment of barriers and facilitators in recruitment will involve the following:Interviews with researchers about patient-reported reasons for joining the study or not;Interviews with researchers about barriers to recruitment in the primary care setting, and among exercise referral practitioners.

The logic model shown in figure 2 will guide the process evaluation of the intervention. The logic model shows the types of data that will be collected, as well as the causal pathways proposed to contribute to behaviour change and intervention outcomes.

The assessment of intervention engagement and acceptability will involve the following:Semi-structured interviews with up to 10% of the intervention group participants. A purposeful sampling framework will be used to ensure participants with a range of characteristics (gender, age, underlying health condition and trial centre) are invited to take part. Interviews will be conducted at different stages of participation in the trial, with each individual being invited to participate in telephone interviews and if appropriate follow-up interviews (up to a maximum of three telephone interviews over the course of the intervention period (approximately 4 months). Interviews will be recorded and transcribed and personal data or ways of identifying participants removed. Transcriptions will be imported into NVivo for data management purposes. The interview transcripts will be coded and thematic analysis performed to identify key findings. Analysis will initially focus on ‘top level’ themes, reflected in the intervention logic model. Analysis will follow the principles of Framework Analysis.^43^ Further in-depth analysis will also be undertaken in order to ensure emergent data, for example, from longitudinal cases, or condition-specific themes, are explored fully. The focus of the interview questions will be linked to the phase of the intervention, and seek to identify the perceived value of the ‘Welcome Pack’ and contents in helping to access e-coachER, the overall web-based support and each of the Steps to Health, in terms of functionality and utility to support behaviour change. Participants will be asked to identify if and how they thought e-coachER provided support for their ERS, and maintaining physical activity in addition to and beyond the ERS support. Ideas for additions or revisions to e-coachER will be requested. Questions will also focus on the participants’ perceived development of self-regulatory skills (eg, self-monitoring, goal setting) and the extent to which the intervention enhanced a sense of competence, autonomy and relatedness, thereby linking back to the aims and guiding principles of the e-coachER intervention.The researchers will be asked to maintain field notes on any interactions with participants concerning engagement with the intervention, such as any difficulties faced with accessing the intervention website. Semi-structured interviews will be conducted by the qualitative researcher with the researchers at each recruitment site to identify participant barriers and facilitators to using e-coachER.Engagement with the web-based e-coachER support system will be quantified. Metrics such as whether the participant registered, how far they progressed in the seven Steps to Health, visits to and time spent on different web pages and within each of the respective Steps, number of times step counts or amount of physical activity (eg, MVPA) were entered into e-coachER (ie, self-monitoring) and number of times goals were achieved and reviewed.Changes in the process measures (see above) (eg, self-efficacy/confidence to be and importance of being physically active) from baseline to 4 and 12 months follow-up will be assessed and compared between intervention arms.Mediation analysis to determine the extent to which changes in the process measures mediate the effect of the intervention on changes in physical activity at 4 and 12 months.

### Data handling

Data will be collected and stored in accordance with the Data Protection Act 1998/General Data Protection Regulation 2018.

#### Subject numbering

Following receipt of expression of interest, each patient will be allocated a unique number and will then be identified in all study-related documentation by their identification number and initials. A record of names, addresses, telephone numbers and email addresses linked to participants’ identification numbers will be stored securely on the study database for administrative purposes only.

#### Data collection

Data will be recorded on study-specific paper-based case report forms (CRFs) by the local researcher, and participants will complete a paper-based questionnaire booklet comprising validated and non-validated self-report outcome measures (listed in table 1).

Accelerometers will be configured for use prior to issue to participants by the local researcher at baseline and the CTU thereafter, using GENEActiv software. A recording window of 10 days, recording at 75 Hz, will be preset, thus accounting for transits in the post while optimising the battery life of the device.

Accelerometers received by the CTU following 1 weeks’ wear by the participant will be physically cleaned with liquid detergent (according to manufacturer’s instructions) before data are downloaded via GENEActiv software and linked to participant identification number. Accelerometers will then be issued to other participants in the trial as required.

Data on participants’ uptake of the ERS will be collected via a single use token-based authenticated email sent to participants at 4 weeks post-baseline. This will be a short survey requesting information on whether the participant has attended the initial consultation with the ERS advisor, and predefined reasons for non-attendance status, for example, appointment has been booked but not yet attended.

All persons authorised to collect and record study data at each site will be listed on the study site delegation logs, signed by the Principal Investigator.

#### Data entry

Original CRFs and questionnaire booklets will be posted to the CTU, with copies of the CRF retained at the study site. All data will be double-entered by CTU staff on to a password-protected SQL Server database and encrypted using Secure Sockets Layer. Double-entered data will be compared for discrepancies using a stored procedure and discrepant data will be verified using the original CRF. Incomplete, incoherent, unreadable or other problem data in the CRF pages will be queried by the CTU with study site staff during data entry to ensure a complete and valid dataset. Self-reported data in the questionnaire booklet will not be queried with participants.

The CTU may complete further validation of data items, perform logical data checks and raise further data queries after data collection has been completed. The final export of anonymous data will be transferred to statisticians for analysis after all data cleaning duties have been performed by the CTU.

### Data analysis plan

All analyses will be carried out using a detailed a priori statistical analysis plan. Analyses will be reported in full and in accordance with the Consolidated Standards of Reporting Trials (CONSORT) guidelines.^44^ Recruitment, uptake of the ERS, engagement with the intervention, outcome completion rates and study withdrawal will be reported (with 95% CIs). Baseline characteristics in the two trial arms will be reported.

The primary analysis will compare complete case outcomes between intervention and control arms groups according to the principle of intention to treat (ie, according to original randomised allocation) at 12 months adjusting for baseline outcome values and stratification and minimisation variables (recruitment site and disease indication).

Secondary analyses will be undertaken to compare groups at follow-up across all follow-up points (ie, 4 and 12 months) using a mixed effects repeated measures approach. In addition, we will seek to undertake secondary per-protocol analyses using a complier average causal effect approach to examine the impact of different levels of the adherence to the intervention.

Accelerometry data will be analysed with bespoke software to classify data into levels of physical activity intensity using accepted cut-points. Standard operating procedures will be applied to make a decision about dealing with missing data.

The primary analysis model will be extended to fit interaction terms to explore possible subgroup differences in intervention effect in stratification and minimisation variables and the predefined baseline characteristics. As not formally powered, these subgroup analyses will be regarded as exploratory and hypothesis-generating.

Sensitivity analysis, using multiple imputation and assuming unobserved measurements are missing at random will be conducted for both primary and secondary analyses to assess the likely impact of missing data on the primary and secondary outcomes at 12 months. Contemporary mediational analysis methods^45^ will be used to explore the impact of process outcomes identified in the planned intervention components, including engagement, use of behaviour change techniques and motivation and processes of change (eg, self-efficacy, autonomy, relatedness).

No interim analysis of primary or secondary outcomes is planned. No adjustment of p-values will be made to account for multiple testing, although the implications of multiple testing will be considered when evaluating the results of the analyses. Analysis of the primary outcome will be performed prior to all other analyses. All analyses will be undertaken using STATA V.14.2.

Checks will be undertaken to assess the robustness of models, including assessment of model residual normality and heteroscedasticity.

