### Randomisation

On receipt of the baseline accelerometer at the CTU after 1 week’s wear, participants will be randomised. Randomisation will be stratified by site with minimisation by the participant’s perceived reason for their referral to the ERS (ie, weight loss, diabetes control, reduce blood pressure, manage lower limb osteoarthritis symptoms, manage low mood/depression) and by self-reported IT literacy level on a visual analogue scale (ie, lower or higher confidence). To maintain allocation concealment, the minimisation procedure will retain a stochastic element and will be conducted using a secure, password protected web-based system.

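### The covariates listed for the primary model omit IT literacy, one of the two minimisation factors, so the listed model does not match the randomisation; any effect is small and conservative

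*Protocol article*

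**What the plan says.** Randomisation section: "Randomisation will be stratified by site with minimisation by" two factors. The first is the participant's "perceived reason for their referral to the ERS", in five categories: "weight loss, diabetes control, reduce blood pressure, manage lower limb osteoarthritis symptoms, manage low mood/depression". The second is added with "and by self-reported IT literacy level on a visual analogue scale (ie, lower or higher confidence"). The section also states that "the minimisation procedure will retain a stochastic element"; the probability is not given.

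Data analysis plan section: the primary analysis is a complete-case comparison at 12 months by randomised group, "adjusting for baseline outcome values and stratification and minimisation variables (recruitment site and disease indication"). IT literacy is not named as a covariate anywhere in that section. Later in the section the primary model is extended with interaction terms to "explore possible subgroup differences in intervention effect in stratification and minimisation variables and the predefined baseline characteristics", this time without a list.

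Aim and objectives section: IT literacy is among the possible moderators of the intervention's effect that the trial intends to explore.

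**The concern.** The general phrase in the primary-analysis sentence, stratification and minimisation variables, covers IT literacy. The bracket that spells the phrase out does not. The bracket carries no mark that it is only an example, so one sentence supports two different primary models.

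The usual principle is to analyse by the factors that the allocation balances on. When a prognostic factor is balanced by design and then left out of a linear model, its variance stays in the residual. The treatment estimate varies less between repetitions of the trial than its reported standard error implies. The interval is then somewhat too wide, the test rejects a true null less often than 5%, and some power is given up. IT literacy could plausibly be such a factor in a trial of a web-based intervention, but the documents offer no evidence on how strongly it relates to MVPA.

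There is also a difference of label: the analysis refers to disease indication, the randomisation to the participant's perceived reason for referral.

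**Working it through.** **Inputs from the protocol article.** Effect size 0.35 SD, 413 participants, two-sided 5%, 88% power with 20% attrition or 90% with 16%, and SD 104 to 113 min (Determination of sample size); 1:1 allocation (Abstract); the factors and covariates quoted above.

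**The plan's own figure first.** Per arm, n = 2(1.96 + z)² / 0.35².
- 88% power: z = 1.175, n = 160.5, so 161 per arm and 322 in all; 322 / 0.80 = 403.
- 90% power: z = 1.282, n = 171.5, so 172 per arm and 344 in all; 344 / 0.84 = 410.

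Both are within 3% of 413. Conversely, 413 × 0.80 = 330.4 analysed, or 165.2 per arm, gives 0.35 × √(165.2/2) = 3.181 and power Φ(3.181 − 1.96) = 88.9%. With 16% attrition the power is 90.3%. The stated sample size reproduces, and its calculation claims no gain from covariates.

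**Effect of leaving IT literacy out.** Let R² be the share of 12-month MVPA variance that IT literacy explains after the other covariates. The documents do not give it; 2%, 5% and 10% are assumptions. Put k = 1/√(1 − R²). Under perfect balance:
- reported SE / true SE = k
- type I error = 2(1 − Φ(1.96k))
- power without IT literacy = Φ((3.181 − 1.96)k), because the estimate's true SD shrinks even though the reported SE does not
- power with IT literacy = Φ(3.181k − 1.96)

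| Assumed R² | SE too large by | Type I error | Power without | Power with | Difference (points) |
|---|---|---|---|---|---|
| 0 | 0% | 5.0% | 88.9% | 88.9% | 0 |
| 2% | 1.0% | 4.8% | 89.1% | 89.5% | 0.4 |
| 5% | 2.6% | 4.4% | 89.5% | 90.4% | 0.9 |
| 10% | 5.4% | 3.9% | 90.1% | 91.8% | 1.7 |

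Holding power without IT literacy at 88.9% in every row would overstate the loss, since the balance that lowers the type I error also tightens the estimate.

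**Scale in minutes.** At the middle SD of 108.5, the 95% half-width without IT literacy is 1.96 × 108.5 × √(2/165.2) = 23.4 min. With it, the half-width is 22.9 min at R² = 4% and 22.3 min at R² = 9%.

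**Imperfect balance.** A simulation used 413 participants, 3 sites, 5 referral reasons, 2 IT levels, minimisation within site with an assumed probability of 0.8, 20% random loss and 12,000 runs per setting. For the model without IT literacy:

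| R² | Reported SE / empirical SD | Formula | Type I error | Formula |
|---|---|---|---|---|
| 0 | 1.00 | 1.00 | 0.050 | 0.050 |
| 1% | 1.01 | 1.005 | 0.049 | 0.049 |
| 4% | 1.03 | 1.021 | 0.045 | 0.046 |
| 9% | 1.03 | 1.048 | 0.045 | 0.040 |
| 16% | 1.07 | 1.091 | 0.037 | 0.033 |

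With IT literacy in the model the ratio was 0.99 to 1.01 and type I error 0.049 to 0.055. The Monte Carlo error of a rejection rate is about √(0.05 × 0.95 / 12,000) = 0.002, so the simulation confirms direction and order of size rather than the third decimal. At the larger R² values, a random element and attrition make the effect smaller than the perfect-balance formula says.

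**The case against.** The strongest defence is that the omission may not be real. The governing words cover all minimisation variables, the bracket may be an incomplete gloss, and the article defers to a detailed a priori statistical analysis plan that is not shown. That stands as far as intent goes: a reader might infer that the trial team decided to drop IT literacy, and the text does not establish this. It does not remove the point. The article does not leave the covariates open; it lists them, and the list disagrees with its own Randomisation section.

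Three further inferences are tempting and are not supported.
- **That the primary intervals are too wide.** This holds only if IT literacy is prognostic given baseline MVPA, site and referral reason. No document says so; with no association the interval is correct.
- **That the analysis uses a different disease variable from the one minimised on.** Participants can have several conditions, so a diagnosis-based covariate could differ from the perceived reason. But the allocation categories are themselves condition-based, and disease indication is probably shorthand for them. This is a matter of matching labels.
- **That IT literacy drops out of the interaction analyses, or enters them without its main effect.** The interaction sentence again refers to the minimisation variables, the objectives name IT literacy as a moderator, and an interaction model ordinarily carries the main effect.

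It is also fair to say that planned power is not at risk: in every scenario above, power without IT literacy is at least 88.9%.

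**Conclusion.** The mismatch between the listed covariates and the randomisation factors is real and can be checked from the text alone. Its numerical consequence is conditional and small: for an assumed R² of 2% to 10% under perfect balance, a standard error 1.0% to 5.4% too large, type I error of 4.8% down to 3.9%, and 0.4 to 1.7 points of power forgone. It tends to be less with imperfect balance and is nil if IT literacy is not prognostic. The error is conservative: no bias in the estimated difference, no excess of false positives, no change to 413 or to the stated 88% power. This is a minor correction to the primary-analysis wording, not a threat to the trial's conclusions. Its main value is that it removes a choice between two primary models.

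**What to change.** State the primary model in full: 12-month weekly MVPA on arm, baseline MVPA, site, perceived reason for referral and IT-literacy category, the last three exactly as held by the randomisation system. Use the same term for the referral factor in both sections. Carry the same covariates into the secondary, imputation and interaction models. If leaving IT literacy out is intended, say so and give the reason.

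The cost is one sentence and one two-level covariate. Minimisation needs that value for every participant, so adding it loses no complete cases. The wording should be settled before the allocation code is broken.
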